## 5. Sample size

Since the study will done in two preselected municipalities and the distribution and number of TB microscopy services in these municipalities is largely predefined by the routine health care conditions under which we wish to observe the impact of a new diagnostic tool, the number of units for this study is fixed at 14. Since also the expected baseline TB notification rate for these units is fixed, the effective sample size can only be varied by varying the observation period.

Sample size calculations were based on the following principles and assumptions:

- Units serve a population of on average 500,000 inhabitants.
- The incidence rate of diagnosed pulmonary TB is on average 100/100,000 inhabitants per annum.
- Of the diagnosed TB cases, on average 50% are diagnosed as sputum-smear positive.
- The level of statistical significance is 0.05 (alpha error).
- The power for detecting an observed difference as statistically significant is 0.80 (Beta error)
- The coefficient of variation is 0.25 (for lack of situational data).
- The additional design effect due to the stepped-wedge design DEFFsw (a consequence of the imbalance between the two comparison groups except halfway the observation period) is between 1.5 and 2.0.

The number of units needed was estimated using the formula by *Hayes and Bennett* [[23]](#endnote-24)for a unmatched group-randomized trial with two arms in which the study outcome is based on disease rates [1]:

C = 1 + (zα/2+zβ)2[(λ0+λ1)/y + k2(λ02+λ12)]/(λ0-λ1)2

in which C is the number of clusters (units) in each study arm, zα/2 and zβ are the standard normal distribution vales, λ0 and λ1 are the disease rates in the baseline and the intervention arms, respectively, arm, y is the person-years in each unit, and k is the coefficient of variation. The additional design effect due to the stepped-wedge design was taken into account by inflating in this formula the standard normal distribution values of 1.96 for α=0.05 and 0.84 for β = 0.80 by multiplying these by the assumed design effect DEFFsw, as proposed by *Moulton et al*.

In our calculations C was fixed at 14, λ0 and λ1 were set as indicated below and the additional design effect was varied between 1.5 and 2.0, so that the parameter that changed as a result was y. Assuming fixed population sizes this thus resulted in a minimum observation period for each study arm in a classical group-randomized trial with concurrent allocation of the intervention and equal size, which was then multiplied by 2 to arrive at the total observation period for the stepped-wedge design. We repeated this for total observation periods of 24, 20, 16, 12 and 8 months.

The sample size was calculated based on an average rate of diagnosis of 50/100,000 per annum for the baseline period, and a baseline diagnosis rate of 10/100,000 per annum with bacteriological confirmation through culture (i.e. 20% of sputum smear-negative cases), with a total of 60/100,000 per annum. The minimum diagnosis rate that can then be observed as significantly different from this baseline rate would range from 93/100,000 for a duration of 24 months to 95/100,000 for a duration of 8 months assuming DEFFsw=1.5, and from 110/100,000 for a for duration of 24 months to 112/100,000 for a duration of 8 months assuming DEFFsw=2.0 (figure 2). Varying the average size of the populations served by each unit from 350,000 to 750,000 has very limited effect on these estimates. For a more conservative, “worst case” scenario of a baseline rate of 20/100,000 (i.e. 40% of all smear-negative TB is bacteriologically confirmed in the baseline period), the corresponding figures would range from 109 to 128/100,000, respectively.

Based on an observed increase in the rate of diagnosed bacteriologically confirmed cases irrespective of smear status. Here we assumed for the baseline period an average rate of bacteriologically confirmed diagnosis 50/100,000 per annum for smear-positive TB of, plus the 10/100,000 mentioned above for smear-negative TB, totaling to 60/100,000 per annum. The minimum diagnosis rate that can then be observed as significantly different from this baseline rate would range from 93/100,000 for a duration of 24 months to 95/100,000 for a duration of 8 months assuming DEFFsw=1.5, and from 110/100,000 for a for duration of 24 months to 112/100,000 for a duration of 8 months assuming DEFFsw=2.0 (figure 3). Also here, varying the average size of the populations served by each unit from 350,000 to 750,000 has very limited effect. For a more conservative, “worst case” scenario of a baseline rate of 20/100,000 (i.e. 40% of all smear-negative TB is bacetriologically confirmed in the baseline period), the corresponding figures would range from 109 to 110/100,000, and from 128 to 130/100,000, respectively (data not shown). These calculations show that for a duration of 8 months (i.e. each unit contributes on average 4 months to the baseline period and 4 months to the intervention period) the study power is definitely sufficient to detect as statistically significant a relevant increase in the rate of diagnosis or notification of bacteriologically confirmed smear-negative TB, i.e. an approximately 2-fold increase depending on DEFFsw. We also calculated the sample size for the detection of a significant increase in sputum-smear negative cases. Considering 50/100,000 per annum for smear-positive TB of, plus the 10/100,000 mentioned above for smear-negative TB, totaling to 60/100,000 per annum during the observation phase. The minimal increase to be detected as stastitically significant would be 17/100,000 for 24 months and 18/100,000 for 8 months, assuming a 1.5 DEFFsw; and 20 to 22/100,000 assuming aDEFFsw of 2.0.

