In Brazil, smear examinations are widely available for patients with TB suspicion, free of charg for patients, in public health units. Culture is only recommended by the National TB Control Program (NTCP) in patients with previous history of TB, in PLHA, when treatment failure is suspected by the end of the second month of treatment, in difficult to obtain specimens, in extrapulmonary TB and in contacts of a resistant TB index case. Since sputum smear examination has a low sensitivity, the bulk of smear-negative TB diagnoses is made clinically without microbiological confirmation.[[5]](#endnote-6) In addition, despite the official recommendations, according to data from the NTCP, only 72% of new cases and only 17% of retreatment cases perform culture.Error: Reference source not found If added to cases with a negative sputum smear, at present, only one third of Brazil’s notified new cases are bacteriologically confirmed. It is estimated that 20% of these cases are not true TB cases (false positive diagnosis), resulting in delayed diagnosis of the true disease and unnecessary exposure to hepatotoxic antituberculous drugs. In conclusion, the limitations of the currently available tests for TB result in delayed diagnosis and unnecessary treatment.[[6]](#endnote-7),[[7]](#endnote-8)

In order to increase the detection of sensitive TB and to accelerate the diagnosis of resistant TB, the NTCP had the plan, in 2010, to implement universal culture (for every patient suspect of TB). Nevertheless, at present, the national laboratories that perform culture and DST, the state LACENs (Laboratório Central Noel Nutels) cannot absorb this workload, a great investment would be necessary.

A novel test platform has been developed, which is based on rapid real-time PCR. The all-in-one cartridge method allows use outside specialized laboratories. A version for detection of *M. tuberculosis*, the GeneXpert, has been developed with funding by FIND, the Foundation for Innovative New Diagnostics. Controlled trial in over 1700 TB suspects showed a sensitivity of 92.2%, representing a significant gain vis-à-vis sputum smears. In sputum smear negative samples, the sensitivity of GeneXpert® is 72.5% in one sample and reaches 90.2% in three samples.[[8]](#endnote-9)-[[9]](#endnote-10)[[10]](#endnote-11)[[11]](#endnote-12)[[12]](#endnote-13)[[13]](#endnote-14)[[14]](#endnote-15)[[15]](#endnote-16)[[16]](#endnote-17)[[17]](#endnote-18)[[18]](#endnote-19)[[19]](#endnote-20)

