# **III. STUDY POPULATION AND DESIGN**

## 1. Study population

The study will look at the *health system* rather than at individual clinics, i.e. will in both municipalities include a diagnostic center together with all clinics that drain on it. The reason is that introduction of new diagnostics may lead to changes in referral which the study should capture.

In **Rio de Janeiro** there are 10 health districts belonging to the municipal network, each with at least one facility with TB smear examination capacity that serves the other health facilities in the district. If sputum smear examination is requested by the clinic, two specimens are transported to the district microscopy facility for examination. Culture is performed in 4 municipal reference labs: P. Hélio Pellegrino, P. Carlos Alberto Nascimento, H. Municipal Rafael de Paula Souza e H. N. Sra do Loreto. DST is performed in four specialized reference labs that operate outside the Municipal network: Federal University Hospital, Hélio Fraga TB Reference Center, State Lab and Fiocruz. In addition TB is diagnosed in a number of general and emergency hospitals.

Rio de Janeiro has  an estimated population of 6,291,773  in 2008 , and a total TB notification of 7,349 cases among people living in the city (overall notification rate 2008 of 116.8/100,000), including 3,401 Smear-positive pulmonary cases (notification rate 54.1 /100,000), 1,614 smear-negative pulmonary cases (notification rate 25.7/100,000), and 910 extrapulmonary cases (notification rate 14.5/100,000). Of all reported TB cases, 65% are diagnosed by primary care units.[[21]](#endnote-22) In Rio de Janeiro, all 11 laboratories will use the new technology for diagnosisng TB, as detailed in the Methods section.

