In **Manaus** there are several basic (primary) care units with TB smear microscopy capacity. The city network is divided into 4 areas, each with a main lab that handles TB diagnostics for the area, but with large variation in numbers of specimens examined and yet limited coordination. Other important diagnostic centers are the Policlinic Cardoso Fontes (PCF) and de Fundação de Medicina Tropical do Amazonas (FMTAM). PCM is the main TB diagnostic center in the city and receives most referrals for TB diagnosis and treatment; it detects 50% of the TB cases in Manaus. FMTAM is an HIV in- and outpatient clinic that handles most TB-HIV co-infection cases. TB culture is done at two sites: LACEN-AM and FMTAM. Manaus in 2008 had an estimated population of 1,73 million, and a smear-positive total TB notification of 1,775: 1,480 pulmonary and 295 extrapulmonary cases (overall notification rate 94/100,000), including 957 (64.7%) smear-positive pulmonary cases 427 smear-negative pulmonary cases (28.9%), and 96 cases in whom no smear test was performed.

During the roll out pilot, the GeneXpert assay will be introduced at each of the 11 laboratories that provide sputum smear microscopy in Rio de Janeiro: this will be the most logical and feasible location for a diagnostic procedure that is to replace smear examination. Since there is no overlap between the health districts in terms of smear microscopy services, this also provides clear separation between allocation units (see Study design, below). This will make calculation of rates based on population denominators straightforward.

In Manaus the GeneXpert assay will be introduced at 3 sites: PCM, FMTAM and one of the 4 TB labs in the city network: the Basic Health Care unit of the Eastern District (Disa Leste). These three sites together take approximately 70% of the current smear examination load in the city. In order to limit overlap in catchment population between these sites and increase coverage of the entire city population, primary care clinics will as much as possible divert, for the duration of the pilot project, their smear examination requests to one of these three sites.

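### The 50/50 smear split in the sample size does not match the classified 2008 notifications, and power for all confirmed pulmonary TB (endpoint 1) is below 80% on those data; endpoint 3 keeps about 98%

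*Protocol*

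**What the plan says.** Protocol, III.5 Sample size, assumes 100 diagnosed pulmonary cases per 100,000 a year and "Of the diagnosed TB cases, on average 50% are diagnosed as sputum-smear positive". It then takes 10 per 100,000 as the 20% of smear-negative cases confirmed by culture, so smear-negative disease is set at 50 and the confirmed baseline at 50 + 10 = 60. The other inputs include "The level of statistical significance is 0.05 (alpha error", "The power for detecting an observed difference as statistically significant is 0.80 (Beta error" and "Units serve a population of on average 500,000 inhabitants". The smallest detectable confirmed rate is given as 93 (24 months) to 95 (8 months) at DEFFsw 1.5, and 110 to 112 at DEFFsw 2.0. Directly after these figures the section concludes that "the study power is definitely sufficient to detect as statistically significant a relevant increase"; the sentence goes on to name confirmed smear-negative TB and a roughly two-fold increase. A separate smear-negative calculation, giving 17 to 22, follows it.

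Protocol, III.1 Study population, reports for 2008 in Rio de Janeiro 3,401 smear-positive cases (54.1 per 100,000) and "1,614 smear-negative pulmonary cases (notification rate 25.7/100,000". For Manaus, with 1.73 million inhabitants, it reports "957 (64.7%) smear-positive pulmonary cases 427 smear-negative pulmonary cases (28.9" per cent), plus 96 cases without a smear. The Introduction states that GeneXpert sensitivity in smear-negative samples "is 72.5% in one sample and reaches 90.2% in three samples".

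**The concern.** GeneXpert replaces smear, so it raises the count of confirmed cases mainly by confirming disease that smear misses. The size of the smear-negative pool therefore sets how far endpoint 1 can rise. The plan takes that pool as 50 per 100,000, while the classified data for the same two cities give about half of that. The protocol does not reconcile the two.

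Endpoint 1 is listed first, it matches the case-detection objective in II.2, and III.6 bases the 8-month duration on this section. If its power is low and the plan does not say so, a non-significant result could be read as absence of impact in a study meant to inform national adoption.

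**Working it through.** **Formula, as printed in III.5.** C = 1 + [DEFFsw(1.96 + 0.84)]²[(λ0+λ1)/y + k²(λ0²+λ1²)]/(λ0−λ1)², with C = 14 and k = 0.25. At 8 months each arm has 4 months, so y = 500,000 × 4/12 = 166,667 person-years. I use it without endorsing its fit to a stepped-wedge design.

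**The plan's own figures.** Solving for λ1 from λ0 = 60:

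| DEFFsw | 24 months | 8 months | Printed |
|---|---|---|---|
| 1.5 | 92.8 | 94.5 | 93, 95 |
| 2.0 | 109.2 | 111.7 | 110, 112 |

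From λ0 = 10 the formula gives 16.1 to 17.6 and 19.2 to 21.4. These match the printed 17 to 18 and 20 to 22 as rates, although the text calls them increases.

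**2008 rates, both cities pooled.** Population 6,291,773 + 1,730,000 = 8,021,773.
- Smear-positive: (3,401 + 957)/8,021,773 = 54.33 per 100,000.
- Classified smear-negative: (1,614 + 427)/8,021,773 = 25.44.
- Rio cases in no listed category: 7,349 − 3,401 − 1,614 − 910 = 1,424.
- Upper bound for smear-negative: (1,614 + 427 + 1,424 + 96)/8,021,773 = 44.39.

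**Baseline and attainable rate for endpoint 1.** Baseline = smear-positive + 0.20 × smear-negative. Attainable = smear-positive + s × smear-negative, with s = 0.725 (one sample) or 1 (every smear-negative case confirmed).
- Plan: 50 + 10 = 60; 50 + 36.25 = 86.3; 100.
- Classified 2008: 54.33 + 5.09 = 59.4; 54.33 + 18.44 = 72.8; 79.8.
- Upper bound: 54.33 + 8.88 = 63.2; 54.33 + 32.18 = 86.5; 98.7.

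**Power at 8 months.** Power = Φ(q/DEFFsw − 1.96), where q = √{13(λ1−λ0)²/[(λ0+λ1)/y + k²(λ0²+λ1²)]}.

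Example, 59.4 to 72.8, in units of 100,000 with y = 1.6667: 132.2/1.6667 = 79.3; 0.0625 × (59.4² + 72.8²) = 551.8; q = 13.4 × √13/√631.1 = 1.92. Power is Φ(1.28 − 1.96) = 25% at DEFFsw 1.5 and Φ(0.96 − 1.96) = 16% at 2.0.

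| Endpoint and split | λ0 to λ1 | DEFFsw 1.5 | DEFFsw 2.0 |
|---|---|---|---|
| 1, plan, 72.5% | 60 to 86.3 | 62% | 40% |
| 1, plan, all confirmed | 60 to 100 | 88% | 65% |
| 1, classified 2008, 72.5% | 59.4 to 72.8 | 25% | 16% |
| 1, classified 2008, all confirmed | 59.4 to 79.8 | 46% | 28% |
| 1, upper bound, 72.5% | 63.2 to 86.5 | 50% | 32% |
| 1, upper bound, all confirmed | 63.2 to 98.7 | 79% | 54% |
| 3, classified 2008, 72.5% | 5.1 to 18.4 | above 99% | 98% |

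The baseline hardly moves with the classified data (59.4 against 60), nor does the detectable rate at 8 months (about 94 and 111). What falls is the attainable rate.

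**The case against.** Four stronger readings are tempting, and the protocol does not support them.

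*That the sufficiency sentence makes a false claim about total confirmed TB.* It names smear-negative TB, and for that endpoint the claim survives the correction. III.4 also calls endpoint 3 the measure where the largest effect is expected. What stands is that the sentence follows, and appears to rest on, the 60-to-95/112 figures. Those are ratios of 1.6 to 1.9. The smear-negative calculation, whose ratios of 18/10 and 22/10 fit the stated two-fold increase, comes only afterwards.

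*That the split alone puts the detectable rates out of reach.* Under the plan's own split the attainable rate at 72.5% sensitivity is 86.3, already below 95, and 112 exceeds the whole assumed pool of 100. The coefficient of variation and the multiplication of the z values by DEFFsw keep the detectable rate high. The 2008 data make an existing weakness worse.

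*That the 2008 data fix the smear-negative pool at 25.* In Rio, with 11 of the 14 units, 7,349 − 910 = 6,439 cases are not extrapulmonary. That is 102.3 per 100,000, of which 3,401/6,439 = 52.8% are smear-positive, close to the plan's inputs. The smear status of 1,424 of these cases is not given. This may explain the assumption for Rio. It does not carry over to Manaus, where all 1,480 pulmonary cases come to 85.5 per 100,000, 64.7% of them smear-positive.

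*That 79.8 is a hard limit.* GeneXpert may detect patients never diagnosed under smear, and III.3 allows repeat testing after a negative result. The protocol gives no estimate of the extra cases. III.4 also says that 10–15% of diagnosed cases are not notified. If this affects both smear groups alike, dividing by 0.90 or 0.85 raises the classified total to 89–94. It also raises the baseline to 66–70 and the detectable rate to 104–110 (DEFFsw 1.5), so power stays near 25% and 16%.

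**Conclusion.** The point holds as a planning input that disagrees with the protocol's own classified data, and as unstated weak power for endpoint 1. On the 2008 figures, power for endpoint 1 at 8 months runs from 16% (25 smear-negative, 72.5% sensitivity, DEFFsw 2.0) to 79% (44 smear-negative, all confirmed, DEFFsw 1.5). It passes 80% only with the plan's own split, every smear-negative case confirmed, and DEFFsw 1.5. Endpoint 3 is not in doubt, at about 98% or more.

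These figures rest on the printed formula with k = 0.25, 20% culture confirmation at baseline, and the 72.5% sensitivity applied to notified smear-negative cases. They leave out cases newly found by GeneXpert, which would raise power, by an amount the protocol does not allow one to estimate. They do not show that endpoint 1 cannot reach significance.

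**What to change.** In III.5, replace the 50/50 split with the 2008 figures (about 54 smear-positive and 25 smear-negative per 100,000, with a range to 44 for unclassified and untested cases), or justify keeping it. State baseline, expected rate and power separately for endpoints 1 and 3, and say that power for endpoint 1 is below 80% on these data. If extra cases found by GeneXpert are counted on, give the assumed number. Move the sufficiency sentence after the smear-negative calculation, rest it on that, and label the 17 to 22 as rates.

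The cost is a recalculation and a less favourable stated power for endpoint 1. No units or months are added; lengthening to 24 months would lower the plan's detectable rates only from 95 to 93 and from 112 to 110.

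### The endpoint 1 detectable rates come from an unmatched two-arm formula that does not fit the within-unit design, so 80% power for an attainable all-case effect is not shown

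*Protocol*

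**What the plan says.** Protocol III.5 (Sample size) fixes the number of units at 14 and lets only the observation time vary. Its inputs include 500,000 people per unit, a coefficient of variation k of 0.25 and an additional stepped-wedge design effect DEFFsw of 1.5 to 2.0. On the disease rate it states: "The incidence rate of diagnosed pulmonary TB is on average 100/100,000 inhabitants per annum". Half of the cases are taken as smear-positive.

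The formula is the one for an "unmatched group-randomized trial with two arms in which the study outcome is based on disease rates", with C units in each arm and C set to 14. DEFFsw multiplies the "standard normal distribution values of 1.96 for α=0.05 and 0.84 for β = 0.80".

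For confirmed TB of any smear status the baseline is 60 per 100,000 (50 smear-positive plus 10 culture-confirmed smear-negative). The smallest detectable rates are said to "range from 93/100,000 for a duration of 24 months to 95/100,000 for a duration of 8 months assuming DEFFsw=1.5" and from 110 to 112 at DEFFsw 2.0. With a worst-case baseline of 70 they are 109 to 110 and 128 to 130. For confirmed smear-negative TB alone the section gives 17 to 18 and 20 to 22 per 100,000, described as the smallest increase. It concludes that 8 months is enough, and words this for confirmed smear-negative TB and a roughly two-fold rise. III.6 then sets 8 months on the basis of III.5.

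III.2 says that every unit contributes time to both conditions. III.10 adjusts the Poisson model for unit and month. III.3 tests one GeneXpert specimen, with an optional repeat after a negative result. The Introduction gives the yield: "In sputum smear negative samples, the sensitivity of GeneXpert® is 72.5% in one sample", rising to 90.2% with three.

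**The concern.** A detectable rate is useful only if the intervention could produce it. Most of the endpoint 1 figures lie above the total number of cases that the same section assumes to be diagnosed, and all of them lie above what one specimen would be expected to confirm. They also hardly change when the duration triples, which suggests that a term unrelated to observation time dominates. Endpoint 1 measures the first objective (II.2). If its power statement rests on a formula for another design, a null result cannot be interpreted from it, and the reader cannot tell what 8 months buys for that endpoint.

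**Working it through.** **1. Reproducing the protocol.** The printed formula is C = 1 + z²[(λ0+λ1)/y + k²(λ0²+λ1²)]/(λ0−λ1)². Here C = 14, k = 0.25 and z = (1.96+0.84) × DEFFsw. The person-years per unit and arm are y = 500,000 × half the duration, i.e. 500,000 at 24 months and 166,667 at 8 months. Solving for λ1 (per 100,000):

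| Baseline | DEFFsw | 24 months | 8 months | Stated |
|---|---|---|---|---|
| 60 | 1.5 | 92.8 | 94.5 | 93, 95 |
| 60 | 2.0 | 109.2 | 111.7 | 110, 112 |
| 70 | 1.5 | 108.2 | 109.8 | 109, 110 |
| 70 | 2.0 | 127.2 | 129.7 | 128, 130 |
| 10 (smear-negative) | 1.5 | 16.1 | 17.6 | 17, 18 |
| 10 (smear-negative) | 2.0 | 19.2 | 21.4 | 20, 22 |

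Rounded up, every stated figure is recovered. The last two rows show that 17 to 22 are detectable rates. The increases over the baseline of 10 are 6.1 to 7.6 and 9.2 to 11.4.

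**2. What dominates.** At 60 to 94.5 and 8 months:
- Poisson term: (60+94.5)×10⁻⁵/166,667 = 0.93×10⁻⁸.
- Between-unit term: 0.0625 × (60²+94.5²)×10⁻¹⁰ = 7.83×10⁻⁸, or 89% of the sum.

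Duration acts only on the Poisson term, so tripling it moves the answer by about 2 per 100,000. The between-unit term treats a unit's baseline and intervention months as if they came from different units. With unit in the model, stable differences between units drop out.

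**3. What is attainable on the protocol's inputs** (50 smear-positive and 50 smear-negative per 100,000):
- One specimen: 50 + 0.725×50 = 86.25.
- Keeping the 10 culture-confirmed cases and adding 72.5% of the other 40: 60 + 29 = 89.
- Three specimens: 50 + 0.902×50 = 95.1.
- Every diagnosed case confirmed: 100.

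**4. Power by the protocol's own method, 8 months.** For 60 to 86.25 the bracket is 7.78×10⁻⁸, and the standard error is √(7.78×10⁻⁸/13) = 7.73×10⁻⁵. The ratio is 26.25/7.73 = 3.39. Power is Φ(3.39/1.5 − 1.96) = 62% and Φ(3.39/2 − 1.96) = 40%. For 60 to 100 it is 88% and 65%.

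**5. A calculation that fits the design.** This is a Poisson log-rate model with 14 unit effects and month effects, in which two units switch at each of seven monthly steps over 8 months. The expected baseline count is 500,000 × 60/100,000/12 = 25 per unit-month. Each unit-month has variance 1/mean + CV² on the log scale, where CV is residual unit-month variation. The protocol gives no such CV, so the values are assumptions. No further DEFFsw is applied, because the model already contains the steps.

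| Residual CV | Detectable rate from 60 | Power, 60 to 86 | Power, 59 to 73 |
|---|---|---|---|
| 0 | about 72 | above 99% | about 92% |
| 0.10 | about 73 | above 99% | about 84% |
| 0.25 | about 80 | about 94% | about 53% |

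The last column uses III.1 for Rio de Janeiro: "1,614 smear-negative pulmonary cases (notification rate 25.7/100,000", with smear-positive cases at 54.1. Baseline: 54.1 + 0.2×25.7 = 59. Intervention: 54.1 + 0.725×25.7 = 73. Manaus gives a similar smear-negative rate (427/1.73 million = 24.7 per 100,000).

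At 24 months (eight three-month periods, same CV per unit-period) the detectable rates are about 67, 69 and 77.

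**The case against.** The strongest reply has four parts.

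- **The sums are right.** This stands: every figure reproduces, so this is a point about method and power, not arithmetic.
- **Not all the rates are unattainable.** This stands for 93 to 95, which are below 100 and about equal to the three-specimen 95.1, where the protocol's formula gives 81% power at DEFFsw 1.5. III.3 allows a repeat test, and III.4 also counts culture. Moreover, 100 is the currently diagnosed rate, not a biological limit. The protocol quantifies no gain above it, however, so 109 to 130 remain unexplained.
- **The 8 months rest on smear-negative TB.** This stands. From 10 per 100,000 the formula detects 17.6 to 21.4 at 8 months, well within 0.725×50 = 36. A reader might infer that the duration has no support at all, but the section's conclusion is worded for this endpoint.
- **The formula errs on the safe side.** This stands on the protocol's rates. A reader might infer from 62% and 40% that the trial is underpowered for endpoint 1. The documents do not support that, since those percentages come from the ill-fitting formula and the within-unit model gives far higher power.

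Two limits also apply to the local scenario. Rio's listed categories leave 7,349 − 3,401 − 1,614 − 910 = 1,424 cases unclassified (22.6 per 100,000). If all were smear-negative pulmonary TB, the rate would be 25.7 + 22.6 = 48.3, close to the assumed 50. And longer observation gains only about 3 to 5 per 100,000 in the within-unit model, so the weak effect of duration is only partly due to the formula.

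**Conclusion.** The point holds as a should-fix matter of design and power. The endpoint 1 calculation uses an unmatched formula in which between-unit variation supplies about 89% of the variance, although each unit is its own control and the analysis adjusts for unit and month. It yields detectable rates of 109 to 130 against 100 assumed diagnosed cases, and of 93 to 95 against a one-specimen expectation of 86 to 89. The 80% power is an input to these figures, and no attainable one-specimen effect is shown to reach it.

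This does not show that power is too low. On the protocol's rates a fitting calculation detects about 72 to 80 and gives about 94% power or more for 60 to 86. The open question is the local smear-negative rate: at about 25 per 100,000, power runs from about 92% (CV 0) to 53% (CV 0.25). That range rests on assumed residual CVs, equal unit sizes of 500,000, one-specimen sensitivity, 20% culture confirmation at baseline, and leaving out the unclassified cases.

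**What to change.** In Protocol III.5:

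- Replace the all-case calculation by a stepped-wedge variance with unit and month effects, seven steps of two units, and Poisson plus residual unit-month variation.
- Report detectable rate ratios and power for endpoint 1 over a range of residual CV (for example 0 to 0.25) and of smear-negative rates (for example 25 to 50 per 100,000).
- Remove or explain detectable rates above 100 per 100,000.
- Relabel 17 to 22 per 100,000 as detectable rates for confirmed smear-negative TB, not increases.
- State in III.5 and III.6 which endpoint the 8-month choice rests on.

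The cost is one rewritten section, with no change to units or data collection. The downside is that the stated power for endpoint 1 may look less favourable once local smear-negative rates are used.

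### The detectable effect for smear-negative TB carries the wrong baseline and label: 17–22/100,000 are detectable rates from a baseline of 10, not increases on 60

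*Protocol*

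**What the plan says.** Protocol III.5 fixes the inputs and sizes the study with a cluster-trial formula, "C = 1 + (zα/2+zβ)2[(λ0+λ1)/y + k2(λ02+λ12)]/(λ0-λ1)2". It notes "In our calculations C was fixed at 14" and solves for the intervention rate that can be told apart from the baseline rate.

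The section reports three sets of results:

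- **All bacteriologically confirmed TB, baseline 60/100,000** (50 smear-positive plus 10 smear-negative): minimum detectable rate 93 (24 months) to 95 (8 months) at DEFFsw 1.5, and 110 to 112 at DEFFsw 2.0.
- **A worst case with 20 instead of 10 confirmed smear-negative:** 109 to 110, and 128 to 130.
- **Smear-negative TB.** The starting rate is described as 50 for smear-positive TB, "plus the 10/100,000 mentioned above for smear-negative TB, totaling to 60/100,000 per annum during the observation phase". The result follows: "The minimal increase to be detected as stastitically significant would be 17/100,000 for 24 months and 18/100,000 for 8 months" at DEFFsw 1.5, and 20 to 22 at DEFFsw 2.0.

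Just before the third set, the section concludes that 8 months give enough power for confirmed smear-negative TB, "i.e. an approximately 2-fold increase depending on DEFFsw". Protocol III.4 names confirmed smear-negative TB as the endpoint on which the largest impact is expected. III.6 sets the 8 months on the basis of the sample size section.

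**The concern.** Two statements in one section cannot both be true. From a baseline of 60, a detectable rate of 93–95 or 110–112 means an increase of 33–35 or 50–52. A few lines later, with the starting rate again put at 60 and the method unchanged, the minimal increase is 17–18 or 20–22.

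Taking the figures as increases on 10 does not help. It would mean reaching 27–32/100,000, a 2.7- to 3.2-fold rise, which disagrees with the roughly 2-fold conclusion just above.

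At stake is the only detectable effect in rates per 100,000 that the protocol gives for the endpoint it expects to move most. Anyone who carries the printed increase into a report or a later design would be wrong by about a factor of two or more.

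**Working it through.** **Inputs (all from Protocol III.5).** z = 1.96 and 0.84, sum 2.80, each multiplied by DEFFsw (1.5 or 2.0). C = 14, so C − 1 = 13. k = 0.25 ("The coefficient of variation is 0.25 (for lack of situational data"). Population 500,000 per unit. Each arm gets half the total duration, so y = 500,000 × (T/2)/12: 500,000 person-years for T = 24 months and 166,667 for T = 8.

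**Equation solved for λ1:**

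13 = (2.80 × DEFFsw)² × [(λ0+λ1)/y + k²(λ0²+λ1²)] / (λ1−λ0)²

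**Step 1. Reproduce the plan's figures.**

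| Baseline λ0 (per 100,000) | DEFFsw 1.5, 24 mo | 1.5, 8 mo | 2.0, 24 mo | 2.0, 8 mo | Stated |
|---|---|---|---|---|---|
| 60 | 92.8 | 94.5 | 109.2 | 111.7 | 93, 95, 110, 112 |
| 70 (50 + 20, worst case) | 108.2 | 109.8 | 127.2 | 129.7 | 109, 110, 128, 130 |
| 10 | 16.1 | 17.6 | 19.2 | 21.4 | 17, 18, 20, 22 (called increases) |

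Rounded up, all twelve match. The method and the rounding are therefore the protocol's own, and the third row identifies what the smear-negative figures are.

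**Step 2. One cell by hand (λ0 = 10, 8 months, DEFFsw 1.5).** (2.80 × 1.5)² = 17.64. With λ1 = 17.55/100,000:

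- (λ0+λ1)/y = 27.55×10⁻⁵ / 166,667 = 1.653×10⁻⁹
- k²(λ0²+λ1²) = 0.0625 × 4.080×10⁻⁸ = 2.550×10⁻⁹
- 17.64 × 4.203×10⁻⁹ / (7.55×10⁻⁵)² = 13.0, as required

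**Step 3. The increases.**

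- From 60: 32.8 and 34.5 (DEFFsw 1.5); 49.2 and 51.7 (DEFFsw 2.0).
- From 10: 6.1 and 7.6 (DEFFsw 1.5); 9.2 and 11.4 (DEFFsw 2.0). As multiples of baseline these are 1.6 and 1.8, then 1.9 and 2.1.
- Against the printed 17, 18, 20 and 22, the true increases from 10 are 36%, 42%, 46% and 52%.

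**Step 4. Test the literal readings.** With SE² = [(λ0+λ1)/y + k²(λ0²+λ1²)]/13, power is Φ[(λ1−λ0)/(DEFFsw × SE) − 1.96].

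- 60 to 77, 78, 80 and 82: power about 37%, 38%, 29% and 31%, against the planned 80%.
- 10 to 27, 28, 30 and 32: power 98% or more, so these are not minimal increases.

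**Step 5. Try other versions of the formula.** Variants tried were DEFFsw applied to the variance, no +1 term, full duration per arm, 7 units per arm, and populations of 350,000 to 750,000. None gives an increase of 17–22 from 60; the smallest found was 23.9.

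**The case against.** The strongest reply is that this is a slip of wording. The calculation is introduced as concerning smear-negative cases, and the 10/100,000 is mentioned in it. The four numbers are right once read as rates from 10, and the sentence before them gives the effect as about 2-fold. The number of units, the duration, the endpoints and the analysis would all stay as they are. Read as increases on 10, the error even understates what the study can detect.

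Most of this stands, and it limits the point to a wrong baseline and a wrong label. It does not remove the error: the sentence assigns 60, says increase, and contradicts figures a few lines above it. Nor does the phrase observation phase offer a way out. III.7 uses observation period for the smear-examination phase, and the 50 and the 10 that make up the 60 are both baseline rates.

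A reader might infer more: that the study rests on this one power statement, or that the 8-month duration is unsupported. The protocol does not bear that out. The figures for all confirmed TB are power statements too, they correspond to the first endpoint, and they reproduce exactly. From baseline 10 at 8 months the formula gives 1.8-fold (DEFFsw 1.5) and 2.1-fold (DEFFsw 2.0), which agrees with the stated conclusion.

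**Conclusion.** The stated detectable effect for confirmed smear-negative TB is wrong as written. The 17–18 and 20–22/100,000 are minimum detectable rates from 10/100,000, presented as minimal increases on 60. The minimal increases are about 6–8 (DEFFsw 1.5) and 9–11 (DEFFsw 2.0) from 10, or about 33–35 and 49–52 if 60 were really the baseline. The roughly 2-fold conclusion and the 8-month duration stand.

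This rests on the protocol's formula and inputs as given, including k = 0.25 and the assumed DEFFsw of 1.5 to 2.0. Whether that formula and those assumptions suit the design is a separate question, not judged here.

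**What to change.** In the closing smear-negative calculation of III.5, delete the 50/100,000 and the total of 60, and replace the result with wording such as:

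> From a baseline of 10/100,000 per annum of culture-confirmed smear-negative TB, the minimum detectable rate is 17/100,000 (24 months) to 18/100,000 (8 months) for DEFFsw = 1.5, an increase of about 6–8, and 20 to 22/100,000 for DEFFsw = 2.0, an increase of about 9–11 (roughly 1.6- to 2.1-fold).

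Add that the rates are rounded up while the increases come from the unrounded rates, since subtracting 10 from the rounded rates would give 7–8 and 10–12.

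The cost is two corrected sentences. Nothing in the design, duration or analysis changes.
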